#### Process Evaluation

This part of the evaluation will assess what lessons can be learned from the implementation process and what *key ingredients* are replicable to other clinical settings.

##### Evaluation of the Behaviors of Staff Involved in Implementation of CHOICE

The evaluation design is informed by the Normalization Process Theory [39], which provides a pragmatic framework for collecting and analyzing what the staff does in response to changes in the model of care, and the nonadoption, abandonment, scale-up, spread, and sustainability (NASSS) framework [40] will inform the design of the staff interviews. In addition, the Normalization Measure Development questionnaire [41] will be administered to the staff early on in the rollout and later by email at the end of the data collection period.

##### Evaluation of the Factors That Have Facilitated or Hindered the Adoption of CHOICE

An analysis of the findings from the qualitative data sources will be compared with factors known to be important for spread and adoption [40]. This will enable us to understand the factors that facilitate or inhibit the embedding of CHOICE in the care pathway.

##### Assessment of Resource Use and Workforce

As this model is scaled up, it will offer important learnings on how it can be delivered most efficiently and whether the anticipated changes in clinic activity and type (as a consequence of remote care options) have any implications for the clinic workforce. For example, if the reason for clinic attendance is known in advance, as it is requested by the patient, the patient may not need to be seen by a senior audiologist. Data on the workforce at each site, as well as any changes during the project, will be collected and analyzed.

We will examine the economic impact on the clinic activity of implementing the new care model. We will also apply predictive modeling to understand the impact of scaling up the model beyond a target cohort of several thousand patients. The costs associated with the delivery of follow-up activities will be sourced from each site to understand the impact of uptake of remote care.

### Data Analysis

All data analyses aim to answer the 9 primary and secondary research questions. Statistical analyses will be performed using the SPSS Statistics package (version 26; IBM Corp).

#### Quantitative

Descriptive statistics and graphs will be used to present the data. Data will be displayed visually wherever possible to facilitate sharing with various stakeholders. The significance value will be set at *P*=.05, including Bonferroni corrections for multiple comparisons where appropriate. All repeated-measures data will be compared at baseline and follow-up using analysis of variance to examine any changes in empowerment, hearing, and quality of life in the participants. Surveys will be analyzed at the baseline and follow-up time points using inferential statistical analyses. The choices of participants in the DCE will be subjected to conditional logit model analysis using the *survival* package of the R programming language.

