**Patients**									
	Patient impact (engagement)	1		Quantitative		CHOICE^a^ web app data: number of log-ins, time spent on CHOICE, uses of self–device adjustment (if appropriate), and uses of home hearing check		All data	
	Patient impact (quality)	1		Quantitative		Number of errors in CHOICE, adverse events, and missed issues		All data	
	Patient impact	1		Quantitative		Survey about use of follow-up care (consequences for travel cost, time, hours off work, and child care [including accompanying person])		Once at patient focus group or interview	
	Patient impact	1		Quantitative		NHS^b^ Friends and Family Test		Minimum of twice: baseline (on registration) and after using CHOICE for several months	
	Patient impact	1		Qualitative		Focus groups		Once: planned but unable to happen because of the COVID-19 pandemic	
	Patient impact	1		Qualitative		One-on-one interviews		Once: for patients who prefer one-on-one interviews or if focus groups cannot occur; toward the end of the project	
	Patient empowerment	2		Quantitative		PAM^c^ questionnaire and CI-EMP^d^ questionnaire		Baseline (on registration) and 6 months following registration or end of the project—whichever comes sooner	
	Patient hearing	2		Quantitative		Home hearing check results		All data	
	Patient change in empowerment, hearing, and quality of life	2		Quantitative		Global ratings of change questionnaire		Baseline (on registration) and 6 months following registration or end of the project—whichever comes sooner	
	Patient health-related quality of life, including hearing	2		Quantitative		HUI3^e^ questionnaire		Baseline (on registration) and 6 months following registration or end of the project—whichever comes sooner	
	Patient health-related quality of life	2		Quantitative		EQ-5D-5L^f^ questionnaire		Baseline (on registration) and 6 months following registration or end of the project—whichever comes sooner	
	Patient preference of service delivery	2		Quantitative		Discrete Choice Experiment questionnaire		Baseline (on registration) and 6 months following registration or end of the project—whichever comes sooner	
	Patient confidence and experience	4 and 5		Quantitative		R-Outcomes surveys		Baseline (on registration) and every 6 months; some participants may choose to complete an optional, shorter questions set more often	

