**Figure 2 figure2:**
[figure not shown]
The 5 elements of the discrete choice experiment.

Each attribute had 3 levels that described different approaches and degrees of remote care; for example, the choices for who decides when the next clinic appointment will be *the implant clinic*, *the patient,* or *the implant clinic (however, the patient can request appointments when required)*. The experiment was constructed using the mix and match design method [37], as implemented in the *support.CEs* package for the R statistical environment [38]. The experimental design was organized into 2 blocks to reduce the number of questions each participant had to complete, and patients will be randomly assigned to complete either block 1 or block 2. The design requirements of 5 attributes per alternative, 2 alternatives per choice question, and 2 experimental blocks resulted in the allocation of 9 discrete choices per block. The role of the DCE is to help us learn about how the different elements of the care pathway interact to shape participant preferences for remote care compared with the usual pathway. It is possible that the preferences that patients have for remote care could relate to their outcomes, and we will explore these relationships using exploratory correlational analyses.

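### The choice experiment's conditional logit makes no stated allowance for repeated answers by one patient; with default standard errors, a combined remote-versus-usual contrast could look too precise

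*Protocol article*

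**What the plan says.** The Data Analysis section (Quantitative) of the protocol article names both estimator and software: "The choices of participants in the DCE will be subjected to conditional logit model analysis", with the survival package of R as the software. It adds no clustering, robust variance or random-coefficient term.

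The design is under Patient Outcomes, Quantitative Measures. There are five care-pathway attributes: "Each attribute had 3 levels that described different approaches and degrees of remote care". With two alternatives per question and two blocks, the design "resulted in the allocation of 9 discrete choices per block", and "patients will be randomly assigned to complete either block 1 or block 2". The DCE is meant to show how the elements of the pathway "shape participant preferences for remote care compared with the usual pathway". The same section plans exploratory correlations between patients' preferences for remote care and their outcomes.

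Table 1 lists the "Discrete Choice Experiment questionnaire" at two time points: "Baseline (on registration) and 6 months following registration or end of the project—whichever comes sooner".

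**The concern.** The data are clustered by design. A patient contributes 9 choices if the DCE is completed once and 18 if it is completed twice. With its default variance, a conditional logit treats each choice question as a separate independent stratum and assumes one set of preferences for everyone.

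The plan itself presupposes otherwise. Correlating preferences with outcomes makes sense only if patients differ in how much they like remote care. A patient who likes it in general will lean towards the more remote alternative in question after question, so that patient's answers are correlated.

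At stake is the stated precision of the DCE results. The exposure is greatest when attribute effects are added up into a comparison of a remote pathway with the usual one, because a shared taste pushes all those effects in the same direction.

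**Working it through.** **The plan's own figure.** A main-effects orthogonal array for five 3-level attributes has 18 runs. Split over 2 blocks, 18 / 2 = 9 choices per block, as stated. One completion gives 9 choices per patient; two give 2 × 9 = 18.

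**Inputs for the consequence.** The article gives the attributes, levels, alternatives, blocks and time points. It gives no preference SD and no DCE sample size. Assumed here:
- 100 or 300 patients;
- mean level effects of 0.2 and 0.4 on the logit scale;
- preference SD of 0, 0.5 or 1.0, either independent for each attribute level or as one shared taste for remote care (loading 0.5 on the middle level and 1.0 on the far level);
- for 18 choices, every patient answering the same block twice with unchanged preferences.

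**Method.** With two alternatives, the conditional logit is a no-intercept logit on attribute differences. Each setting had 400 replicates. The ratio shown is the empirical SD of the estimate divided by the model-based SE. Approximate coverage of a nominal 95% interval is 2Φ(1.96 / ratio) − 1; for example, a ratio of 1.33 gives 1.96 / 1.33 = 1.47 and coverage of about 86%. The relative simulation error of an empirical SD is about 1/√(2 × 399) = 3.5%, so ratios between about 0.93 and 1.07 cannot be told from 1.

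**Results (100 / 300 patients).** The all-remote contrast sets all five attributes at the far level against the reference.

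| Choices per patient | Taste | SD | Single attribute, ratio | All-remote contrast, ratio | Coverage of contrast |
|---|---|---|---|---|---|
| 9 | none | 0 | 0.98 / 1.02 | 0.93 / 1.01 | 96.5% / 94.7% |
| 9 | independent | 0.5 | 0.99 / 1.00 | 1.02 / 1.00 | 94.5% / 95.0% |
| 9 | independent | 1.0 | 0.95 / 0.98 | 0.91 / 0.90 | 96.8% / 97.1% |
| 9 | shared | 0.5 | 1.02 / 1.00 | 1.14 / 1.07 | 91.4% / 93.3% |
| 9 | shared | 1.0 | 1.01 / 1.00 | 1.33 / 1.26 | 86.0% / 88.1% |
| 18 pooled | none | 0 | 1.00 / 1.04 | 1.03 / 1.05 | 94.3% / 93.9% |
| 18 pooled | independent | 0.5 | 1.05 / 1.04 | 1.09 / 1.09 | 92.7% / 92.9% |
| 18 pooled | independent | 1.0 | 1.14 / 1.14 | 1.22 / 1.24 | 89.1% / 88.5% |
| 18 pooled | shared | 0.5 | 1.03 / 1.05 | 1.25 / 1.24 | 88.3% / 88.7% |
| 18 pooled | shared | 1.0 | 1.12 / 1.13 | 1.63 / 1.62 | 77.0% / 77.5% |

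The patient-clustered SE was within about 10% of the true SE in every setting (ratio 0.94 to 1.10).

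**Reading the SDs.** Under a shared taste, a patient's all-remote contrast has mean 5 × 0.4 = 2.0 and SD 5 × 0.5 = 2.5 or 5 × 1.0 = 5.0. The larger value is strong heterogeneity. At the smaller one, the one-wave ratio is only 1.07 to 1.14.

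**Second simulation.** A separate run with 300 patients and SDs of 0.5 to 1.0 agreed in direction. The all-remote ratio was 1.01 to 1.45 with a shared taste and 0.97 to 1.01 with independent tastes. Single attributes averaged 1.00 to 1.04 with 9 choices and 1.04 to 1.15 with both waves pooled.

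**The case against.** The strongest reply is that the article names a model and a package in one sentence and says nothing about the variance estimator. A patient-clustered variance is available in that same package, so the sentence is compatible with the analysis recommended here, and a journal article may leave such an option to the full plan. This stands in part. A reader might infer that the plan treats all of a patient's choices as independent and that its intervals are too narrow; the article states neither. What remains is that it fixes a specific model for clearly clustered data, and that this model, run as named with its defaults, does not match the heterogeneity presupposed elsewhere in the article.

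Three further limits stand:

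- **Pooling.** A reader might infer that both waves are pooled, so that patients who stay count twice and tilt the result towards satisfied users. No passage says so. The Quantitative section's sentence on surveys refers to analysis at baseline and at follow-up, which allows separate analyses.
- **The contrast.** A reader might take a summed remote-versus-usual contrast to be the DCE's declared target. The stated aim concerns how the individual elements shape preference; no combined interval or test is specified.
- **Size.** With 9 choices, single attribute effects, the model's direct output, show no material understatement. With tastes that vary independently by attribute, the combined contrast shows none either, and at SD 1.0 the default SE was slightly too large.

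**Conclusion.** The point holds in conditional form. The design gives 9 choices per patient per wave over two waves, and the stated analysis does not account for within-patient dependence. If the default variance is used and patients share a general liking for remote care, intervals will be too narrow and P values too small, mainly for any combined remote-versus-usual contrast. Under assumed preference SDs of 0.5 to 1.0, the true SE of that contrast is roughly 0 to 35% above the model SE with one wave, and further above it if both waves were pooled. None of these percentages rests on a preference SD or DCE sample size from the document, because it gives none.

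Severity is modest. The DCE is ancillary: Table 1 places it under research question 2, but that question asks about empowerment, hearing and quality of life. The link between preferences and outcomes is exploratory, and Proposed Sample Size says the project does not aim at formal hypothesis testing.

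**What to change.** In Data Analysis, Quantitative, state that the conditional logit will be reported with patient-clustered (robust) standard errors, with the patient as the cluster. State also that baseline and follow-up will be analysed separately, or pooled with a time-point interaction and the same clustering. The interaction keeps patients who answer twice from being double-weighted in a single averaged estimate.

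The cost is one model term and one sentence. Intervals become somewhat wider where patients share a taste for remote care and change little elsewhere. The Results section says the research data had not yet been analysed, so the change could still be made before the analysis at that point.

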#### Qualitative

The qualitative data from the patient interviews, staff interviews, and case studies will be thematically analyzed separately but brought together in the triangulation phase using synthesis meetings with different involved investigators. To address the evaluation questions, qualitative findings will be synthesized with the quantitative findings. Both theoretical frameworks applied to this evaluation (NASSS and Normalization Process Theory) will be used to facilitate an understanding of the findings. Qualitative interview data will be coded by 2 qualitative evaluators (Wessex AHSN) using a coding framework based on the NASSS framework. A small sample of transcripts will test and refine the framework with an agreement between the coders. The coding framework and coding of transcripts will use NVivo software. Higher order codes and themes will be presented for scrutiny and sensemaking to the wider evaluation team.

#### Missing Data

We anticipate significant missing data because of the large number of outcomes measured and the clinical population. We expect that data will mostly be missing not at random, as those who discontinue the use of CHOICE or drop out are likely to be those who find it less helpful. This may lead to significant bias. There is likely to be a selection bias, as patients who agree to follow a remote care pathway may not be representative of the population. The same will apply to clinicians: those who want to be involved in implementing CHOICE are likely to be more invested in remote care than their colleagues. Following recommendations [42], when data are ready to be analyzed, inspection will suggest whether statistical methods should be used to handle missing data. As this is an outcome and process evaluation, the extent and pattern of missing data will in itself be significant, with nonresponse bias expected. It is also possible that reporting bias may occur; people with cochlear implants are often so grateful for their treatment that they may provide answers in the direction they perceive that the researchers want.

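### Data are expected to be mostly missing not at random, yet inspection of the collected data is to decide whether any method will handle them

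*Protocol article*

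**What the plan says.** The Missing Data section of the protocol article makes four statements that belong together.

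- Amount: "We anticipate significant missing data because of the large number of outcomes measured and the clinical population". No percentage is given.
- Mechanism: "We expect that data will mostly be missing not at random". The reason offered is that patients who stop using CHOICE or drop out probably got less out of it.
- Consequence: "This may lead to significant bias". Later in the section, "the extent and pattern of missing data will in itself be significant, with nonresponse bias expected".
- Rule: "when data are ready to be analyzed, inspection will suggest whether statistical methods should be used to handle missing data". This follows a reference to published recommendations, which are not at hand.

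The Quantitative section under Data Analysis names one method for change over time: "All repeated-measures data will be compared at baseline and follow-up using analysis of variance to examine any changes in empowerment, hearing, and quality of life". Those three domains are the subject of the second primary research question, which asks whether empowerment rises without detriment to hearing or quality of life. The services outcomes section adds that no control group will undergo the same measures.

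**The concern.** The rule postpones more than the choice of method. It leaves open whether any method is used, and it makes that depend on looking at the data. That does not fit the mechanism stated just before it. Under MNAR, the chance of a missing value depends on the value itself, even after allowing for what was observed. Inspection can describe the extent of missingness and its observed predictors. It cannot show that the unseen values resemble the seen ones, so it cannot support a decision to do nothing.

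If that decision is taken, a baseline-versus-follow-up analysis of variance rests on patients with both measurements. With no comparably measured control group, there is no between-group contrast in which attrition bias might partly cancel. At stake is the answer to the second primary question. The section on participating centers makes any offer of CHOICE to all sites depend on the evaluation results.

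**Working it through.** There is no figure of the plan's own to reproduce: the article gives no dropout rate, no SD and no sample size calculation. What follows sizes the consequence under labelled assumptions.

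**1. Bias of a complete-pairs mean.** Let m be the share without follow-up, and let μR and μN be the mean changes of responders and non-responders. The mean over all enrolled is (1 − m)μR + mμN, so

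bias = μR − [(1 − m)μR + mμN] = m(μR − μN).

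Assumed: m = 0.3 to 0.6, and μR − μN = 0.2 to 0.5 SD of change.

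**2. Comparison with sampling error.** Assumed: 500 complete pairs and a two-sided 95% interval (the article sets the significance level at .05 but does not state sidedness). In SD of change, SE = 1/√500 = 0.0447 and half-width = 1.96/√500 = 0.088. Actual coverage of the all-enrolled mean is Φ(1.96 − bias/SE) − Φ(−1.96 − bias/SE).

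| Missing | Difference (SD) | Bias (SD) | Bias/SE | Coverage of nominal 95% interval |
|---|---|---|---|---|
| 30% | 0.2 | 0.06 | 1.34 | 73% |
| 60% | 0.2 | 0.12 | 2.68 | 23% |
| 30% | 0.5 | 0.15 | 3.35 | 8% |
| 60% | 0.5 | 0.30 | 6.71 | about 0% |

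The bias passes the half-width when the difference exceeds 0.088/0.3 = 0.29 SD at 30% missing, or 0.088/0.6 = 0.15 SD at 60%.

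**3. Cross-check with a normal selection model.** The true mean change is 0, d is the dropout share, and ρ is the correlation between staying and the patient's change. Completer bias = ρφ(z_d)/(1 − d), where z_d is the normal quantile at d.

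- d = 20%: 0.035, 0.105 and 0.175 SD for ρ = 0.1, 0.3 and 0.5.
- d = 40%: 0.064, 0.193 and 0.322 SD.
- d = 60%: 0.097, 0.290 and 0.483 SD.

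Dividing each by d gives the implied difference between responders and non-responders. At d = 40% this is 0.064/0.4 = 0.16 SD for ρ = 0.1 and 0.193/0.4 = 0.48 SD for ρ = 0.3. The difference assumed in step 1 therefore corresponds to roughly ρ = 0.1 to 0.3.

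The chance of a significant change when there is none, at two-sided .05, with assumed enrolment of 100, 400 or 1700 (the last being the article's upper limit for recruitment):

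- d = 40%, ρ = 0.3: 34%, 87% and about 100% (60, 240 and 1020 pairs).
- d = 20%, ρ = 0.1: 6%, 10% and 25% (80, 320 and 1360 pairs).

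The bias does not shrink as numbers grow, whereas the interval does.

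**The case against.** The strongest reply is that this is a condensed article, that the choice of imputation or sensitivity model normally sits in a fuller document, and that the authors disclose the problem frankly. They treat missingness as a finding, plan to report dropouts, and ask leavers for their reasons. Much of that stands: the absence of a named model is not the point. What the article does fix is a rule that lets inspection decide on doing nothing, and neither disclosure nor reasons for leaving bounds the change estimate.

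The documents do not support several stronger readings that a reader might infer.

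- *That the direction of bias is known.* The Missing Data section also blames the number of outcomes and the clinical population, and the Limitations section describes late registration. None of these has an obvious sign.
- *That harm to hearing and quality of life will be understated.* Nothing says that leavers' hearing or quality of life fell. Patients with stable hearing may also see little use in the tool, while a flagged deterioration may bring others into contact with their clinic. In Table 1, home hearing checks are collected as all data, so a missed 6-month questionnaire does not by itself remove a patient's hearing results.
- *That complete pairs are the plan.* This is what the analysis becomes if inspection leads to no method; other outcomes remain open.
- *That results will steer the choice.* The text places inspection before analysis, and it most naturally means inspecting missingness, not effects.

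It can also be said that no missing-data method makes this before-after comparison causal, since the authors expect COVID-19 to be the largest confounder. That is true, but it is no reason to leave a separate, avoidable uncertainty unmeasured.

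**Conclusion.** The concern holds in a limited form. The article states a rule that does not fit its own expectation of mostly MNAR data: inspection cannot establish that such missingness may be left unhandled. If it leads to no method, the empowerment gain would probably be overstated, given who the protocol expects to leave. For hearing and quality of life the direction is uncertain, though detriment could be masked.

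The size is illustrative only. The missing share, the responder difference, the 500 pairs and the correlation are all assumptions. Over the range used, the bias is 0.06–0.30 SD of change against a half-width of 0.088 SD. In the upper part of that range the interval would usually miss the truth. At the low end it would still cover it more often than not, although below the nominal 95%. This is a cheap improvement that should be made; it does not show that the eventual result will be wrong.

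**What to change.** Before the research data are analyzed, replace the decide-by-inspection rule with three prespecified elements.

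1. **A primary analysis of everyone with a baseline, under missing at random.** Use a mixed model, or multiple imputation with baseline score, age, center and, where the records can be linked, digital readiness. App use arises after baseline, so it should enter only as an auxiliary variable in the imputation and not as a covariate in the model for change. State that this step does not address MNAR.
2. **A delta-adjusted tipping-point analysis for empowerment, hearing and quality of life.** Shift non-responders' change stepwise in the unfavourable direction and report the delta at which each conclusion is lost. This is the step that addresses the expected mechanism.
3. **Response rates and baseline scores for responders and non-responders.** Separate administrative loss through late registration from discontinuation of CHOICE. Reporting of dropouts and reasons for withdrawal is already planned, so this extends existing work.

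The Results section says that collection is complete and the research data were not yet analyzed, so on the article's own account the methods can still be fixed before results are seen. The cost is a paragraph and some analysis of data already held. The downside is wider and possibly less favourable estimates.
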